**Ethics and dissemination:**

The study is approved by the local and international institutional review boards in the participating countries (the Joint Research Ethics Committee of the University of Zimbabwe, Medical Research Council of Zimbabwe and University of Zambia Biomedical Research Ethics Committee) and the study sponsor (Queen Mary University of London). Caregivers provide written informed consent for each participant. Findings will be disseminated through peer-reviewed journals, conference presentations and to caregivers at face-to-face meetings.

Strengths and limitations of this studyRigorous collection of longitudinal data on morbidity, mortality and nutritional status during inpatient care and for 48 weeks after initial admission for severe acute malnutrition (SAM) in HIV-positive and HIV-negative children.Laboratory substudies investigating enteropathy, microbiota, metabolomics and immune cell function provide a unique opportunity to understand which pathogenic pathways contribute to SAM and whether these processes normalise with nutritional rehabilitation.High loss to follow-up due to participants returning to home settings following hospital discharge.The clinical heterogeneity of the study participants, including comorbidities such as infections, may make it challenging to identify the specific causes of clinical outcomes.Potential bias in recruiting well-nourished controls only from hospitals will be reduced by inclusion of community-based controls, including well-nourished siblings of children with SAM.

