## Sample sizes

### Observational study

The observational cohort will recruit as many children with SAM as possible during the period of enrolment (July 2016 to March 2018), estimated at 600–800 children (capped at 800 maximum), to assess clinical and nutritional outcomes among HIV-positive and HIV-negative children hospitalised with SAM. Assuming mortality of 15%, overall loss to follow-up of 15% and recruitment target of 800 children, there would be 560 evaluable children at 48 weeks, of whom 224 would have HIV-SAM based on an estimated inpatient HIV prevalence of 40%. This will provide >80% power to detect absolute differences of 17% in binary outcomes between HIV-SAM and HIV-negative children with SAM, and of 0.33 times the SD in continuous outcomes.

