### Immunology substudy

Up to 200 children with SAM and 200 well-nourished controls will be included in a cross-sectional analysis of innate immune cell function during hospitalisation. Assuming similar infectious mortality to a recent Kenyan study (15%),^17^ a cohort of 200 provides 80% power to detect associations between immune profiles and infectious mortality at an OR of 1.7 and two-sided alpha of 0.05. We will aim for 100 children with longitudinal analysis of innate immune cell function at discharge, 12, 24 and 48 weeks post discharge.^17^

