### Observational cohort

The primary comparison will be the clinical and nutritional outcomes of children with HIV-SAM compared with HIV-negative children with SAM. We will review all deaths and adjudicate clinical diagnoses and causes of death to ensure robust and consistent data across sites. We will compare each participant’s clinical management to WHO guidelines to identify any contributory factors in hospital care. Factors associated with outcomes during hospitalisation (eg, mortality, nutritional recovery) will be determined for each group (HIV-SAM and HIV-negative children with SAM) using multivariable analysis (Cox models for time-to-event data, linear models for continuous outcomes). Factors associated with outcomes over 48 weeks post discharge (hospital readmission, morbidity and mortality, relapse, anthropometry, body composition and response to ART) will be determined for each group (HIV-SAM and HIV-negative children with SAM) using multivariable analysis (Cox models for time-to-event data, linear models for continuous outcomes). HIV-positive children with SAM and HIV-negative children with SAM will be included in one model together with the risk factors, and interaction tests will be used to investigate whether associations between risk factors and outcomes differ between the two groups of children. We will evaluate the ability of MUAC at discharge to predict long-term outcomes using receiver-operator-characteristic (ROC) analysis, in the whole cohort and within the subgroups of HIV-SAM and HIV-negative children with SAM. We will then evaluate whether addition of other variables improves the predictive capacity of MUAC (using WHO criteria in those >6 months, and published data for children <6 months^62^) for each group, including body composition, haemoglobin, albumin and CRP, plus CD4%, viral load and timing of ART initiation (HIV-SAM only). We will construct multivariable models and compare them with MUAC alone using the net-reclassification index.

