### Immunology substudy

Integrated profiles of innate immune cell function will be generated for each child using principal components analysis followed by hierarchical clustering.^65 66^ This data -reduction method identifies whether absolute levels of specific markers or relative differences between markers differentiate children into groups. The resulting innate immune profiles will be compared between HIV-SAM, HIV-negative children with SAM and well-nourished groups using univariable tests and multivariable analysis of variance of the principal components.

To address the relationship between immune function and infections, regression analyses will determine whether baseline innate immune profiles (or the individual parameters defining them) are associated with the infectious morbidity or mortality during hospitalisation, using logistic models for binary outcomes and linear models for duration. Key clinical characteristics, including age, sex, oedema and baseline WHZ, will be added to models to investigate their confounding effects. Multivariable stacked regression methods will be used to compare the impact of different factors on severe bacterial infections based on heterogeneity tests.

To determine whether treatment for SAM restores innate immune cell antibacterial function, mixed effects regression models will compare longitudinal changes in individual immune parameters, and the principal components calculated from the weights identified at baseline (which include well-nourished controls). Similarities and differences in longitudinal immune profiles will be compared between groups using non-metric multidimensional scaling.^65 67 68^ This approach will group children according to their composite innate immune function, allowing the duration and variability of immune restoration to be evaluated over the course of nutritional rehabilitation. Binary logistic regression will determine whether innate immune profiles at discharge are associated with morbidity or mortality during follow-up.

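### The immunology substudy uses binary logistic regression for post-discharge mortality, where the parent cohort uses Cox models and loss to follow-up is expected: a small, cheaply removed inconsistency

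*Protocol article*

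**What the plan says.** The Analysis section for the immunology substudy fixes the model for outcomes after discharge: "Binary logistic regression will determine whether innate immune profiles at discharge are associated with morbidity or mortality during follow-up".

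The Analysis section for the observational cohort covers the same outcome in the children from whom the substudy is drawn: "Factors associated with outcomes over 48 weeks post discharge (hospital readmission, morbidity and mortality, relapse, anthropometry, body composition and response to ART" are to be studied with "Cox models for time-to-event data, linear models for continuous outcomes". These are the only two model types named there, and death is not a continuous outcome, so post-discharge mortality falls under Cox.

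On follow-up:
- The sample-size section is written "Assuming mortality of 15%, overall loss to follow-up of 15% and recruitment target of 800 children".
- The strengths and limitations list includes "High loss to follow-up due to participants returning to home settings following hospital discharge".
- The footnote to Table 2 (observational cohort) allows the 48-week visit up to 71 weeks + 6 days. Table 3 (enteropathy substudy) gives only 44 to 52 weeks. The immunology substudy draws children from both.
- The Follow-up and Study outcomes sections describe telephone contact and home visits for children who miss visits, where these can be done.

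On size, the immunology sample-size section includes up to 200 children with SAM in the cross-sectional analysis, and for the later time points it says: "We will aim for 100 children with longitudinal analysis of innate immune cell function at discharge, 12, 24 and 48 weeks post discharge".

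**The concern.** A binary model needs a yes or no for each child over a common period. A child last seen alive at week 12 has neither. Unless outcomes are imputed or children weighted, the child is left out or entered as a survivor. Children whose final visit comes at different times also have different time at risk, which the model does not see. A Cox model uses each child's time up to last contact, and the protocol already uses one for this outcome in the parent cohort.

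At stake is the estimated association between discharge immune profile and later death. If children with poorer profiles are lost more often, or less often, the odds ratio is pushed up or down depending on how lost children are handled. The same deaths would also be summarised as odds ratios in one analysis and hazard ratios in another, without a stated reason.

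**Working it through.** **1. The plan's own figure.** 800 × (1 − 0.15 − 0.15) = 560, and 560 × 0.40 = 224. This reproduces "there would be 560 evaluable children at 48 weeks, of whom 224 would have HIV-SAM". The 15% loss is the article's only numerical planning value for loss in this study; no figure is attached to the logistic analysis itself.

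**2. Simulation set-up.** 1,500 replicates per scenario, with n = 100 and n = 200.
- From the article: 15% loss, and the two sample sizes.
- Assumed: hazard ratio 1.7 per SD of immune score; 15% mortality after discharge (the article's 15% figures are for overall and for infectious mortality); deaths concentrated early; 30% loss as an upper value; loss hazard multiplied by 1, 1.7 or 1/1.7 per SD; loss independent of death given the score.

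Four fits were compared: logistic with no loss, logistic with lost children dropped, logistic with lost children counted as alive, and Cox censored at loss.

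**3. Benchmark.** A log odds ratio has to be judged against the logistic result with no loss. With no loss at all, logistic gave an odds ratio of 1.80 to 1.85 for a hazard ratio of 1.70. The gap, ln(1.804/1.70) = 0.06 to ln(1.845/1.70) = 0.08, is a difference of scale and not bias. So shift = ln(OR with loss / OR without loss).

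**4. Results at n = 200.**

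| Loss | Loss hazard per SD | OR, no loss | OR, dropped (shift) | OR, alive (shift) | Cox HR |
|---|---|---|---|---|---|
| 15% | 1 | 1.804 | 1.809 (+0.003) | 1.798 (−0.003) | 1.701 |
| 15% | 1.7 | 1.806 | 1.929 (+0.066) | 1.712 (−0.053) | 1.701 |
| 15% | 1/1.7 | 1.808 | 1.736 (−0.041) | 1.857 (+0.027) | 1.710 |
| 30% | 1 | 1.822 | 1.824 (+0.001) | 1.792 (−0.017) | 1.706 |
| 30% | 1.7 | 1.836 | 2.150 (+0.158) | 1.650 (−0.107) | 1.718 |
| 30% | 1/1.7 | 1.821 | 1.638 (−0.106) | 1.915 (+0.050) | 1.708 |

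At n = 100 the pattern is the same: the largest shift is ln(1.975/1.845) = 0.068 at 15% loss and ln(2.139/1.809) = 0.168 at 30%. Separate runs with the loss rate doubling or halving per SD at about 14% to 15% loss gave shifts of up to about 0.09. Cox stayed between 1.70 and 1.72 in every scenario of the main simulation.

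**5. Power when loss is unrelated to the profile.**
- n = 200, 15% loss: logistic 76% to 77%, Cox 78%.
- n = 200, 30% loss: logistic 75% to 77%, Cox 78%.
- n = 100, 15% loss: logistic 47% to 48%, Cox 50%.
- n = 100, 30% loss: logistic 43% to 45%, Cox 47%.

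**6. No true effect, n = 200, loss related to the profile.** At 30% loss, dropping lost children gave odds ratios of 1.14 or 0.89 and type I error of about 9%; Cox stayed near 1.0 with about 6%. At 15% loss, dropping gave 1.06 or 0.94 with 6% to 7%, against 6% for Cox.

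**7. Against sampling error.** For a standardised score, the standard error of the logistic coefficient is roughly 1/√[n p(1 − p)]. With p = 0.15 this is 1/√(200 × 0.15 × 0.85) = 0.198 at n = 200, and 1/√(100 × 0.15 × 0.85) = 0.280 at n = 100. A shift of 0.03 to 0.09 is therefore about 0.1 to 0.5 of a standard error. The extreme shifts at 30% loss are 0.158/0.198 = 0.8 and 0.168/0.280 = 0.6 of one. Fewer deaths after discharge would make the standard error larger still.

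**The case against.** The strongest defence has five parts.

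- **Bias needs loss to depend on the immune profile.** The article does not say that it does; it attributes loss to families going home after discharge. This stands. A reader might infer that the expected 15% loss by itself biases the odds ratio, and the first row of the table shows that it does not.
- **Lost children need not be dropped or counted as alive.** Imputation or weighting would work with logistic regression, and an article may leave missing-data handling to a fuller document. This stands too, so the absence of such a rule is not the point made here. The point is the stated model.
- **Tracing recovers some outcomes.** Known vital status is all a binary outcome needs. True in part, but the article makes tracing conditional on feasibility.
- **Cox is not a full cure.** It assumes that censoring is independent of death given the covariates, and the simulation builds that in. If unreported death is itself the reason for loss, Cox is biased as well.
- **The substudy is exploratory, is powered on an odds ratio, and its sentence also covers morbidity.** All correct. The article treats every analysis as exploratory, and binary models are legitimate for binary morbidity outcomes.

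The inconsistency survives these points: one outcome in overlapping children is given two models, and the one chosen for the substudy makes poorer use of incomplete and unequal follow-up.

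**Conclusion.** The choice of logistic regression for post-discharge mortality should be changed, but the expected harm is small. With loss unrelated to immune profile, bias is negligible and the power cost is a few points at most. With loss 1.7 to 2 times higher or lower per SD, the coefficient moves by about 0.03 to 0.09 at the planned 15% loss, and by up to about 0.16 to 0.17 at an assumed 30%, in either direction. These shifts are below one standard error at the planned sample sizes, and the dependence behind them is an assumption.

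Two stronger readings are tempting and are not supported. One takes the gap between the substudy's odds ratios and the cohort's hazard ratios as bias; most or all of such a gap can arise with no loss at all, and the article plans no comparison of the two. The other holds that a stated small number of deaths makes the model unworkable. The article gives no post-discharge death count for the substudy, and any such figure rests on a share borrowed from another cohort with much higher mortality. In-hospital outcomes are not affected, because mortality is reviewed daily until discharge.

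**What to change.** In the Analysis section for the immunology substudy, replace logistic regression for post-discharge mortality with Cox regression from discharge, censored at last contact with known vital status, counting telephone and home-visit tracing as contact. State that this matches the cohort analysis and that it assumes censoring is independent of death given the covariates. Logistic regression may stay for in-hospital outcomes and for binary morbidity outcomes.

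The cost is minimal: one model changes, using follow-up data that the cohort's Cox analysis already needs. No visit, sample or measurement is added. The result is reported as a hazard ratio and no longer as an odds ratio.

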### Immunology substudy

Bacterial infections are common among children hospitalised for SAM^23 48–50^ and mortality is driven by a range of species,^48 50–53^ consistent with generalised defects in innate antibacterial defence. Increased infectious morbidity and mortality persist after discharge from hospital,^10 17 54^ suggesting that restoration of antibacterial immune responses may lag behind nutritional rehabilitation. A recent randomised trial in children with SAM confirmed that deaths following hospitalisation were predominantly due to bacterial infections but were not prevented by daily co-trimoxazole prophylaxis.^17^ Collectively, these observations highlight that children remain vulnerable to infection despite current treatment approaches; targeting persistent immune dysfunction could plausibly reduce infectious mortality after discharge.^24^

Multiple innate and adaptive immune mediators are dysregulated in malnutrition.^24 27 55^ However, few studies have assessed cellular immune function in malnourished children; most existing studies were undertaken decades ago on small cross-sectional cohorts without the benefit of recent advances in immunology techniques.^27^ Immune dysfunction in SAM likely reflects both *intrinsic* defects, whereby immune cells lack capacity to adequately respond to infection, and *extrinsic* defects, where cells have intact antibacterial capacity but are chronically modulated by the systemic pro-inflammatory environment which characterises SAM (ie, heightened pro-inflammatory cytokines^44^ and circulating bacterial antigens^23 56 57^). Systemic inflammation is directly associated with mortality in SAM^23^ and driven by multiple comorbidities, including bacterial translocation from the damaged gut into the blood, subclinical infections and metabolic dysregulation.^44 58 59^ The implications of innate immune cell dysfunction for subsequent acquisition of infections and infectious mortality have not been investigated.

We hypothesise that (i) antibacterial functions of innate immune cells are compromised in SAM due to a combination of intrinsic and extrinsic defects; (ii) innate immune cell function is independently associated with infectious morbidity and mortality during hospitalisation for SAM; and (iii) nutritional rehabilitation only partly restores innate immune cell function, leading to an ongoing risk of bacterial infections post discharge.

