Using blood samples collected at baseline, discharge and 12, 24 and 48 weeks post discharge, the longitudinal relationship between circulating innate immune cell function and bacterial infections will be assessed. The intrinsic phagocytic capacity, secreted cytokine response and maturation state of innate immune cells after culture with bacterial antigens will be assessed. Plasma concentrations of endotoxin and pro-inflammatory mediators will be quantified at each time point and the degree to which these extrinsic factors influence innate immune cell antibacterial function will be assessed via plasma co-culture with innate immune cells from healthy donors. Bacterial infections during hospitalisation will be diagnosed using clinical criteria and blood culture, stool culture and urinalysis where available.

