## Study outcomes and risk factors

The main study outcomes are clinical (mortality, morbidity and relapse of malnutrition) and nutritional (weight, height, MUAC, leg length, head circumference, mid-thigh circumference, skin-fold thickness and body composition by bioimpedance vector analysis) assessed over 48 weeks of follow-up. Mortality is assessed in hospital by daily physician review and, post discharge, through study visits and by telephone where possible for children who are lost to follow-up. Morbidity during hospitalisation is assessed through daily clinical assessments and available hospital laboratory tests. Morbidity after discharge is assessed, first, using daily morbidity diaries, in which caregivers record episodes of illness (lethargy interfering with feeding; respiratory distress; diarrhoea; oedema and fever); second, from caregiver recall and review of handheld medical records at each follow-up visit; and, third, from data collected during hospitalisation for children who are readmitted during the follow-up period. Time-to-recovery from malnutrition will be evaluated during hospitalisation; relapse of malnutrition during follow-up will be categorised as moderate acute malnutrition, uncomplicated SAM and complicated SAM, according to WHO definitions. Nutritional outcomes will be expressed both as continuous variables (attained Z-score and change in Z-score between visits), and as categorical variables (moderate wasting, WHZ<–2; severe wasting, WHZ<–3; stunting, HAZ<–2; severe stunting, HAZ<–3; underweight, WAZ <–2; and microcephaly, head circumference-for-age <–2).

Risk factors will be evaluated at baseline, hospital discharge and over the period of follow-up for associations with clinical and nutritional outcomes. In addition to baseline clinical and demographic factors, the following laboratory parameters will be evaluated: haemoglobin, serum albumin, C reactive protein (CRP), CD4 count and HIV viral load (for HIV-positive children). Haemoglobin, CD4 and HIV-viral load will be measured in real time and the results reviewed during follow-up clinics.

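### Immunology substudy: the follow-up model uses unqualified morbidity or mortality, so it does not directly test the hypothesis about bacterial infection after discharge

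*Protocol article*

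**What the plan says.** Under Substudies, Immunology substudy, the third hypothesis is that "nutritional rehabilitation only partly restores innate immune cell function, leading to an ongoing risk of bacterial infections post discharge". The methods paragraph in that section takes blood from baseline to 48 weeks and says that "the longitudinal relationship between circulating innate immune cell function and bacterial infections will be assessed". The diagnostic criteria given there refer to hospital stays: "Bacterial infections during hospitalisation will be diagnosed using clinical criteria and blood culture, stool culture and urinalysis where available".

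Under Analysis, Immunology substudy, two regressions link immune profiles to clinical events.

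- In hospital, the question is whether baseline profiles, or the parameters behind them, "are associated with the infectious morbidity or mortality during hospitalisation, using logistic models for binary outcomes and linear models for duration".
- After discharge: "Binary logistic regression will determine whether innate immune profiles at discharge are associated with morbidity or mortality during follow-up".

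Study outcomes and risk factors names three sources for morbidity after discharge. The first is a caregiver diary of symptoms ("lethargy interfering with feeding; respiratory distress; diarrhoea; oedema and fever"). The second is caregiver recall with handheld medical records. The third is hospital data from readmissions.

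**The concern.** The hypothesis and the stated longitudinal aim are about bacterial infection. The in-hospital model keeps that restriction and the follow-up model drops it. Read plainly, the follow-up outcome counts any recorded illness or any death.

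Some of what it would count is not infection. Oedema is one of the criteria that define SAM in the Screening section, and relapse of malnutrition is listed as a main outcome in its own right, so a diary entry for oedema may be relapse. Lethargy is non-specific.

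Two misreadings follow. A null result might mean that immune function at discharge is unrelated to later infection, or only that non-infectious events swamped the association. A positive result might be driven by relapse and be read as support for an infection mechanism.

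**Working it through.** **1. Text side by side**

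| Place | Period | Outcome |
|---|---|---|
| Hypothesis (ii) | in hospital | infectious morbidity and mortality |
| In-hospital regression | in hospital | infectious morbidity or mortality |
| Hypothesis (iii), second half | after discharge | bacterial infections |
| Follow-up regression | after discharge | morbidity or mortality, unqualified |

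The first pair matches and the second does not. The first half of hypothesis (iii), partial restoration of immune function, has its own analysis: the mixed effects models of longitudinal change. Only the infection-risk half is affected.

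**2. The plan's own figure**

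Sample sizes, Immunology substudy, gives N = 200, 15% infectious mortality, two-sided alpha 0.05, 80% power and an odds ratio (OR) of 1.7. It does not give the unit of the OR; I assume one SD of a continuous profile score. For logistic regression on a standardised covariate:

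N = (1.96 + 0.842)² / [p(1−p)(ln OR)²]

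With p = 0.15, p(1−p) = 0.1275. The OR detectable at N = 200 is exp(2.802/√25.5) = 1.74, which agrees with 1.7 to one decimal. At exactly 1.70 the formula gives 76% power, or N = 219 for 80%. The figure is reproduced after rounding. It covers infectious mortality only; no power is stated for the follow-up model.

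**3. What pooling would do (illustration)**

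Inputs from the article: OR 1.7, 15%, and 100 children with longitudinal immune data. Assumptions not in the article:

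- the OR of 1.7 and the 15%, given for infectious mortality, are applied to infection after discharge;
- non-infectious events occur with probability q, independently of the profile and of infection;
- the outcome is a yes/no pool of both kinds of event.

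Pooled prevalence: P = 1 − (1 − 0.15)(1 − q). For q = 0.25, P = 1 − 0.85 × 0.75 = 0.3625.

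Pooled log OR, approximately: ln 1.7 × (0.15/P) = 0.531 × 0.414 = 0.220, an OR of about 1.25. Fitting the logistic model to simulated profile scores gives 1.24, used below.

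Power = Φ(√(nP(1−P)) × ln OR − 1.96)

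- Infection alone, n = 100: √12.75 × 0.531 − 1.96 = −0.07, power 47%.
- Pooled, n = 100: √23.1 × 0.214 − 1.96 = −0.93, power 18%.

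Range over the assumed inputs:

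| Infection risk | q | Pooled prevalence | Pooled OR | Power, n = 100 | Power, n = 200 |
|---|---|---|---|---|---|
| 15% | 0 | 15% | 1.70 | 47% | 76% |
| 15% | 25% | 36% | 1.24 | 18% | 31% |
| 15% | 50% | 57.5% | 1.14 | 10% | 15% |
| 15% | 80% | 83% | 1.10 | 5% | 7% |
| 30% | 0 | 30% | 1.70 | 68% | 93% |
| 30% | 25% | 47.5% | 1.38 | 37% | 63% |
| 30% | 50% | 65% | 1.26 | 20% | 35% |
| 30% | 80% | 86% | 1.19 | 9% | 14% |

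Pooling costs power in every row. How much depends on q, for which the article gives no figure.

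**The case against.** The case on the other side is substantial.

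- **Shorthand.** The follow-up wording may simply abbreviate the infectious outcome named a few lines above it, and morbidity and mortality may be meant as separate outcomes. Possible, but the text does not say so, and the restriction is explicit where it is used.
- **Sources of morbidity.** The diary is one of three. Handheld records and readmission data can carry diagnoses, and the in-hospital infection criteria could apply during a readmission. This stands: infection after discharge is not unascertainable. It also makes the fix feasible.
- **Deaths.** All deaths are reviewed and their causes adjudicated, with verbal autopsy where possible. The substudy's background also cites a trial in which deaths after hospitalisation were mostly due to bacterial infection. This stands: dilution of the mortality outcome should be modest.
- **Power figures.** The OR of 1.7 was an effect to be detected for infectious mortality in 200 children. A target of 100 already limits power without any dilution, and the model needs only a discharge profile, so more children may contribute. This stands; the figures are illustrative, and n = 200 is shown for that reason.
- **Condensed article.** Case definitions may sit in the full protocol or analysis plan. Their absence is not the point here; the stated outcome differs from the stated hypothesis.

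A reader might go further and infer that almost every child would be positive over 48 weeks of daily diaries. The article gives no follow-up morbidity rate and does not say that any single diary symptom makes a child a case, so that inference is not supported.

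**Conclusion.** The mismatch is real and narrow. As written, the only model linking immune profiles to events after discharge does not use the outcome that hypothesis (iii) names, so the infection-risk half of that hypothesis is not directly tested. The restoration half is.

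Under the stated assumptions (15% infection risk, 25% independent non-infectious events, n = 100), the OR falls from 1.7 to about 1.24 and power from about 47% to 18%; at n = 200, power falls from 76% to 31%. These figures give direction and rough scale only, and apply mainly to morbidity.

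It would be too much to conclude that the study cannot inform the infection claim at all. Planned records and adjudicated causes of death can identify infectious events, and the opening of the Analysis section declares every analysis exploratory. For that reason the severity is low.

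**What to change.** In Analysis, Immunology substudy:

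- Make infectious morbidity after discharge and, in a separate model, infectious mortality the main follow-up outcomes for the discharge immune profiles.
- Name the sources for classifying them, all already planned: study-clinic assessments, handheld records, readmission data, verbal autopsy, and adjudicated diagnoses and causes of death.
- State that oedema does not count as an infectious event.
- Keep unqualified morbidity and unqualified mortality as secondary outcomes.
- Word conclusions as clinically diagnosed infection, since the article describes culture only for hospital stays and only where available.

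The cost is a change of wording plus the work of classifying events. No new data collection is needed. The downside is some misclassification of infection after discharge, where diagnoses will rest largely on clinical records and caregiver reports.
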